### Adverse events

The number of minor side effects, cases of serious pathology, and serious adverse events will be compared between groups at the end of the study.

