#### Blinding

The results dataset will be stored with the study arm identity blinded by way of a unique code for each study participant. The key to this code will be held (independent of the dataset for analysis) by the independent statistician, the chair of the data monitoring committee (DMC) and the principal investigator (PI). The PI needs to know practice group allocation to conduct the intervention group training workshops. The PI will not be involved in data collection, entry, modification or analysis.

Individual patients will remain blind to the presence of two study arms throughout the course of the trial. Consultation appearance will be similar from a patient perspective, except that intervention arm participants may be provided a FREE booklet and referred to the FREE website. Control arm participants may be given other informational materials (e.g., ACC pamphlet) or be referred to other information sites (e.g., patient.org). Even if a patient perceives he/she is receiving a different approach from previous GP LBP consultations, they will remain blind to the study hypothesis.

All patient participant data submitted on paper surveys will be entered or checked by a research assistant blind to group allocation. Data entered by participants through electronic surveys will be checked for completeness and anomalous responses.

Data cleaning and analysis will be conducted by the trial statistician who is blind to group allocation. Once analysis is complete, the results will be unblinded. To eliminate the risk that the trial statistician may have been inadvertently exposed to practice codes during the conduct of the trial, these will be replaced with new codes in the dataset prior to the trial statistician’s receiving the data. Only the independent statistician and the chair of the DMC will have access to the key for these new codes.

GPs and practices will necessarily be unblinded following group allocation because the need for training means GPs will know whether they are in the intervention or control arm prior to patient recruitment. GPs will be aware of their study allocation when completing baseline measures. This is necessary in order to minimise the time between completing baseline measures and receiving FREE training or starting patient recruitment. The content of the intervention will be unknown to all GPs at the time they complete their baseline questionnaire.

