### Adverse events

The risks to participants in this trial are small, and no serious adverse events or side effects attributable to the treatment provided are expected. Patients and GPs will be encouraged to report all potential adverse events and incidents of serious pathology (and method of discovery) observed amongst trial participants to the research team on a continuous basis during the study, including through each follow-up survey. Adverse event reports will be reviewed by the DMC (detailed below).

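### The safety comparison covers fewer kinds of event than the trial collects and does not separate blinded patient reports from reports by GPs who know their arm

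*Protocol article*

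**What the plan says.** The protocol article has two sections headed Adverse events.

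The one placed before Data monitoring committee deals with collection: "Patients and GPs will be encouraged to report all potential adverse events and incidents of serious pathology (and method of discovery) observed amongst trial participants". Reports come in "on a continuous basis during the study, including through each follow-up survey", and the DMC reviews them. The same section says that "no serious adverse events or side effects attributable to the treatment provided are expected".

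The one placed after GP process measures deals with analysis and is a single sentence: "The number of minor side effects, cases of serious pathology, and serious adverse events will be compared between groups at the end of the study". It does not define a side effect, say who decides what counts as one, or mention the source of the report.

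On who knows what, the Blinding section says "GPs and practices will necessarily be unblinded following group allocation", and of patients "Individual patients will remain blind to the presence of two study arms throughout the course of the trial".

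The Statistical analysis section adds two general rules. Every result is to be given as an effect size with a 95% CI (the risk ratio is one of its examples), and clustering is to be allowed for where appropriate.

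**The concern.** Two things do not fit together.

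- **Scope.** Collection is open to any possible adverse event. The comparison names three categories, and the only one for non-serious events is minor side effects. The collection section itself ties side effects to attribution to treatment. If the term carries that meaning in the analysis sentence, a non-serious event that nobody attributes to care is recorded but enters no comparison. The same holds for an event that is neither minor nor serious.
- **Source.** One reporting channel is scheduled and comes from patients who do not know there are two arms. The other relies on encouraging GPs who do know their arm. The section Intervention group lists, among the goals of FREE, less GP anxiety about screening for pathology and more confidence that movement is safe. Both attitudes could affect whether a GP notices and reports an event.

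At stake is how a difference between arms, or the lack of one, can be read. If reporting differs by arm, the comparison mixes harm with readiness to report. If non-serious events fall outside the categories, the comparison has less to work with. The choice of which events count would then be left until the reports are in hand.

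**Working it through.** The article gives no figure for the safety comparison, so there is none to reproduce. The only figure used below is the recruitment target in Sample size, which does reproduce: 2 × 110 / (1 − 0.20) = 275, or 137.5 per arm if the split is equal.

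**1. Scope, side by side**

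| Kind of event | Collected? | In a compared category? |
|---|---|---|
| Serious adverse event | yes | yes, no attribution condition stated |
| Serious pathology | yes | yes, no attribution condition stated |
| Non-serious, minor, labelled a side effect | yes | yes |
| Non-serious, not labelled a side effect | yes | no, on a literal reading |

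How many events fall in the last row is unknown. As an illustration, assume a 10% risk of a non-serious event: 137.5 × 0.10 = 13.75 events per arm. If 10% to 50% of them are labelled side effects, 1.4 to 6.9 are compared and the rest are not.

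**2. Source**

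Assume the same true risk in both arms. An event is counted if the patient reports it (probability *p*, equal in both arms) or the GP reports it (probability *g*, which may differ), independently of each other. The counted share is 1 − (1 − *p*)(1 − *g*), and the apparent risk ratio is the FREE share over the control share.

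For *p* = 0.5 and *g* = 0.5 versus 0.3: (1 − 0.5 × 0.5) / (1 − 0.5 × 0.7) = 0.75 / 0.65 = 1.15.

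| GP reporting, FREE v control | *p* = 0.3 | *p* = 0.5 | *p* = 0.8 |
|---|---|---|---|
| 30% v 30% | 1.00 | 1.00 | 1.00 |
| 50% v 30% | 1.27 | 1.15 | 1.05 |
| 30% v 50% | 0.78 | 0.87 | 0.96 |
| 50% v 10% | 1.76 | 1.36 | 1.10 |
| 10% v 50% | 0.57 | 0.73 | 0.91 |

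A comparison on patient reports alone stays at 1.00 throughout, provided patients report equally in both arms. The distortion vanishes when GPs report equally and shrinks as patient reporting becomes more complete.

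**3. Denominator**

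Practices, not patients, are allocated 1:1, so patient numbers may differ by arm. At equal risk, assumed arms of 150 and 125 give a ratio of event counts of 150 / 125 = 1.20, and arms of 165 and 110 give 165 / 110 = 1.50. This matters only if counts are compared without denominators, which the effect-size rule in Statistical analysis argues against.

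**The case against.** A reader might infer that the safety analysis is biased, that it uses raw counts, that it merges patient and GP reports, and that it drops events by rule. The article does not support readings that strong.

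- **Raw counts.** The analysis sentence does speak of a number, but the general rule asks for effect sizes with 95% CIs for all results, and a risk ratio has a denominator. Stratification by practice size and pairing of similar practices also work against a large imbalance. This answers most of the denominator point.
- **Attribution.** A side effect is never defined. Set beside serious adverse events, minor side effects may simply mean non-serious events, in which case little or nothing is lost. Nor is it stated that GPs make the attribution: patients report too, and the DMC sees the reports. What stands is that the wording allows both readings and differs from the collection section.
- **Merging.** That the two sources are combined is inferred from silence, and a fuller document may separate them. What stands is that the sentence as printed does not.
- **Bias.** None is demonstrated. All reporting rates above are assumed, and equal GP reporting gives no distortion.
- **Relying on patient surveys alone.** This would be a poor remedy. Serious pathology is likely to be found by clinicians, and FREE aims at GPs' anxiety about screening for it, so the existing between-arm comparison of pathology must stay. Patient reports are not perfect either: FREE aims to lower perceived threat, which could change what patients report, and 20% loss to follow-up is assumed.

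Pain and disability are also compared as outcomes, so a pain flare would not go wholly unseen.

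**Conclusion.** The concern holds in a limited form. The categories fixed for comparison do not match what is collected, and the comparison does not distinguish blinded from unblinded reporters. Read literally, a non-serious event not judged a side effect is collected and left out of the comparison. Serious adverse events and serious pathology are kept.

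The comparison is open to differential reporting by GPs, of unknown direction and size. Over the assumed range the apparent risk ratio runs from 0.57 to 1.76 with no true difference, and it is 1.00 if GPs report equally. These values rest on equal true risk, equal patient reporting, independent reporting by patient and GP, and a count that accepts either source. None of these comes from the article. They show that the weakness could matter, not that it does.

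It is worth correcting because the data are already collected and only the wording has to change.

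**What to change.** Rewrite the analysis sentence under Adverse events so that it:

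1. compares the proportion of enrolled patients in each arm with at least one adverse event of any severity, regardless of attribution, as an effect estimate with 95% CI under the general rules in Statistical analysis;
2. presents a comparison based on the blinded patient-survey reports separately from GP-reported events;
3. keeps the between-arm comparisons of serious adverse events and of serious pathology from all sources, and shows each by reporter as well.

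Counting patients with at least one event also prevents double counting when patient and GP report the same event.

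The cost is in wording and tables only. Collection and DMC review stay as they are. There are two drawbacks. More unrelated background events will appear in the tables, and survey-based figures will miss patients lost to follow-up, so the number of patients with survey data should be shown beside the number enrolled in each arm.

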### Sample size

For 80% power to detect a between-group difference of 2.5 RMDQ points (the minimal clinically important difference) at 6 months, assuming SD of 6.0 [67] at a *p* value < 0.05 significance level, an individually randomised trial would require 91 patients per group. This has been inflated to 110 patients per group after adjustment for GP cluster effects (assuming a GP intra-cluster correlation coefficient at a conservative 0.05 and, on average, five patients per GP completing the trial). We aim to recruit 275 patient participants to allow for 20% loss to follow-up.

This design requires 22 GPs per study arm. To account for potential zero recruitment by some GPs, we will recruit 30 GPs per study arm. To further account for patient loss to follow-up (assumed ~ 20% of patients per GP) we will ask GPs to recruit seven patients. This gives a maximal potential sample size of 210 patients per study arm if all GPs recruit an average of 7 patients (total sample size = 60 GPs, 420 patients). Sample size calculations were performed using Stata 12 software (StataCorp, College Station, TX, USA).

### Trial governance

This trial has a trial management committee, a broader trial steering committee and an independent DMC. Roles and responsibilities are described in Additional file 6.

### Publication and dissemination

The results of this study will be disseminated regardless of the magnitude or direction of the effect. Results will be presented in four publications:Main outcome report including the primary outcome together with main secondary and economic outcomesDetailed health economic evaluationDetailed process evaluationQuantitative mediation analysis exploring the mechanisms by which FREE might improve patients health

The study results will be provided to the general public and the general medical community through publication in peer-reviewed journals and presentations at conferences. The study results will be provided directly to study participants through email and through the www.lowbackpain.co.nz website. During the trial, this web address will be directed to a site providing study information appropriate for both control and intervention group participants; results will not be published on this site until after the trial has been completed.

## Discussion

A number of tools exist to classify patients presenting with LBP and allocate treatment on the basis of risk of poor outcome [68, 69]. These have been found to have acceptable predictive ability for disability outcomes but poor predictive ability for persistent pain [70]. Encouraging GPs to simply apply these screening tools and plan subsequent referred care on the basis of risk profiles misses the opportunity for a positive therapeutic encounter delivered by the GP at the point on entry into the health system. Even if a GP is to base treatment decisions on a classification process, there is still a need to ensure this first interaction with a health practitioner is delivered in an optimal manner and aids rather than impedes future care. Because FREE is delivered by a GP within normal consultation time, it does not add cost to an episode of care. Therefore, if FREE is found to be effective and does not increase other costs, it may be a cost-effective method of improving LBP care.

In a previous study in which Dutch GPs were trained to explore and address psychosocial factors in patients who had subacute LBP, researchers did not find any clinically relevant benefits [71]. Jellema et al. [72] concluded that this was because GPs were only moderately successful at identifying psychosocial factors and postulated that 20-minute consultations were insufficient for restructuring patients’ dysfunctional beliefs. The FREE approach differs from the intervention of Jellema et al. in three key ways. Firstly, it aims to restructure the basic GP consultation rather than providing it by way of an additional appointment. This makes the approach appear to be standard practice rather than an add-on, allows the earliest possible intervention, minimises the risk of the GP unwittingly increasing patient threat or fear through their usual practice [73], and ensures that a consistent approach can be used in any subsequent encounters. Secondly, FREE bases the exploration of psychosocial factors around the identification and minimisation of factors which increase patient threat in relation to their back pain rather than including all potential psychosocial influences which may overwhelm GPs [33]. Thirdly, it also provides the patient with a booklet and website which support and reinforce the information provided by the GP.

### Limitations

FREE was initially planned to be delivered during the first consultation which someone receives for an episode of acute LBP, and this study was designed to explore the effect of FREE in this population. The study population was expanded to include people with LBP of any duration for two reasons. Firstly, presentation rates of eligible patients to the first recruitment sites was unacceptably low and indicated that recruitment targets would not be met within time frames that were acceptable to either participating practices or the project budget. Secondly, feedback from participating GPs indicated that these restrictive recruitment criteria excluded most of the patients with LBP they commonly saw. Consequently, the generalisability of study findings was likely to be limited. The revised recruitment criteria are similar to those used in previous LBP primary care research [67]. A sensitivity analysis of the main outcomes will be performed restricted to the original study population of participants with acute LBP.

GPs will complete baseline measures post-randomisation (but prior to receiving training). Training requires that all participating GPs in a practice attend a 4-h training session together. Although it would be preferable to have all GPs complete baseline measures prior to randomisation, this is not possible, given the lead-in time required to schedule and co-ordinate training sessions with the practices. GPs will be aware of whether they will receive training, but they will not be aware of the content of the intervention when they complete baseline measures. It is possible that knowledge of group allocation could affect GPs’ responses when completing baseline measures; however, it is considered more important that these be completed close to when training is received and patients are recruited. GP measures are not the trial’s main outcome, and patients are recruited while blind to group allocation.

## Trial status

This is protocol version 2 (amended 8 December 2016). GP participants were recruited between 6 July and 8 August 2016. Patient participant recruitment began on 23 September 2016 and concluded on 31 July 2017.

## Abbreviations

ACC: Accident Compensation Corporation
Back-PAQ: Back Pain Attitudes Questionnaire
BCT: Behaviour change technique
DMC: Data monitoring committee
EMR: Electronic medical record
EQ-5D: EuroQol five dimensions
FREE: Fear Reduction Exercised Early
FTE: Full-time equivalent
GP: General practitioner
HC-PAIRS: Health Care Providers’ Pain and Impairment Relationship Scale
LBP: Low back pain
LBPinGP: Low Back Pain in General Practice
NNT: Number needed to treat
NDRS: Numeric Disability Rating Scale
NPRS: Numeric Pain Rating Scale
OCC-Q-LBP: Otago Costs and Consequences Questionnaire for Low Back Pain
PHO: Primary healthcare organisation
PI: Principal investigator
QALY: Quality-adjusted life-year
REDCap: Research Electronic Data Capture
RMDQ: Roland-Morris Disability Questionnaire
RR: Relative risk
SPIRIT: Standard Protocol Items: Recommendations for Interventional Trials
WTP: Willingness to pay
